#### **13.4.2 Time to Failure of Secondary Survival Endpoints**

The time to disease-free survival (DFS) will be measured from the date of randomization to the date of events (see section 11.3.4). The survival distribution of DFS will be estimated by the Kaplan-Meier method. We want to show that the hazard rate of Arm 1 ( $\lambda_1$ ) will be lower than that of Arm 2 ( $\lambda_2$ ) in the DFS distribution. This hypothesis will be tested using a log-rank test statistic at a significance level  $\alpha = 0.025$ . The treatment effect on the other types of failure (disease-specific survival, local progression, distant failure, PSA failure, second clinical relapse,

second PSA relapse) may impact the observable measures of outcomes and other competing risks may dilute the sensitivity. We will use the cause-specific hazard rate approach to consider the competing events. Freidlin and Korn showed that the cause-specific hazard rate approach is better than other approaches (for example, the cumulative incidence method in most cases. The log-rank test on the times to the specific type of failure, which considers the presence of competing events, will be used to test whether the survival/failure rates of these secondary endpoints in Arm 1 are better than that of Arm 2 for each hypothesis at a significance level of 0.025. In this approach, patients who experience other failure first are censored. To analyze whether treatment effect is independently associated with secondary survival endpoints while adjusting for other factors, a Cox proportional hazards regression model was used for DFS and Fine and Gray's regression model were used for the other types of secondary survival endpoints. Both unadjusted and adjusted hazard ratios and the respective 95% confidence interval will be computed. At least the treatment arm, the stratification variables (PSA, grade, nodal status), age, and race (as appropriate) will be adjusted for in this analysis.

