#### **13.4.1. Analysis of the Primary Endpoint**

The number of events is based on the specific primary hypothesis that the overall survival rate of Arm 1 is higher than that of Arm 2. The results from D'Amico's paper with a similar patient group showed an 8-year overall survival rate of 61% in patients treated with RT only. Based on this result, we assume the control arm (i.e., Arm 2) will have an 8-year overall survival rate of 60%, which translates to a yearly hazard rate of 0.0639. The study is designed to show an absolute improvement of 7% in the 8-year overall survival rate in Arm 1 (i.e., an 8-year overall survival rate of 67%), which translates to a yearly hazard rate of 0.0501. Assuming an exponential distribution for overall survival, 716 deaths are required to detect a 21.6% relative reduction in the yearly death rate with 90% statistical power using a one-sided log-rank test at the 0.025 significance level.

A final analysis will be performed when 716 deaths occur. The time to overall survival will be measured from the date of randomization to the date of the death due to any cause (see section 11.3.10). We assume that the distribution of overall survival for each arm is an exponential distribution. We want to show that the hazard rate of Arm 1 ( $\lambda_1$ ) will be lower than that of Arm 2 ( $\lambda_2$ ) in the overall survival distribution. The following hypotheses are tested.

$$H_0: \lambda_2 \leq \lambda_1 \quad \text{vs.} \quad H_A: \lambda_2 > \lambda_1$$

The survival distribution of overall survival will be estimated by the Kaplan-Meier method. This hypothesis will be tested using a log-rank test statistic at a significance level  $\alpha = 0.025$ . In addition, the Cox regression model will be used to compare the treatment differences. Both unadjusted and adjusted hazard ratios and their respective 95% confidence interval will be computed. At least the treatment arm, the stratification variables (PSA, grade, and nodal status), age, and race (as appropriate) will be adjusted for in this analysis.

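### Six secondary failure endpoints are tested on the cause-specific hazard, but the only regression named for them is Fine and Gray's model, so the reported ratio can differ from the tested effect

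*Protocol*

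**What the plan says.** Everything at issue stands in one paragraph, Protocol section 13.4.2. For every secondary time-to-event endpoint other than disease-free survival (DFS), it takes the following steps.

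- It adopts the cause-specific hazard "approach to consider the competing events", and supports the choice with a cited methods paper that "showed that the cause-specific hazard rate approach is better than other approaches", giving the cumulative incidence method as the example of an inferior one in most cases.
- It fixes the test: "The log-rank test on the times to the specific type of failure, which considers the presence of competing events, will be used to test" each endpoint at 0.025, and "In this approach, patients who experience other failure first are censored".
- It then turns to regression: "To analyze whether treatment effect is independently associated with secondary survival endpoints while adjusting for other factors", a Cox model "was used for DFS and Fine and Gray's regression model" for the rest. The text runs on from the model to the estimates: "were used for the other types of secondary survival endpoints. Both unadjusted and adjusted hazard ratios" are promised with 95% confidence intervals, and the sentence on the ratios names no model.

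Cox regression is thus named for DFS only. Nothing says that the Fine and Gray ratio is on a different scale from the log-rank test, or that it is meant as a supplement.

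**The concern.** A log-rank test that censors competing events tests whether the cause-specific hazards are equal. Fine and Gray's model keeps patients with a competing event in the risk set, so its null is equal cumulative incidence. The two nulls coincide only if treatment does not change the competing events. The plan does not expect that in general: section 13.3 sets out to detect a 33% lowering of failure rates, and section 13.4.1 hypothesises fewer deaths ("716 deaths are required to detect a 21.6% relative reduction in the yearly death rate").

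For overall survival and DFS, test and estimate are paired (log-rank with Cox). Only the six competing-risk endpoints break the pairing, and they do so with a model from the class that the paragraph has just argued against. A cause-specific p-value may then stand beside a subdistribution ratio labelled a hazard ratio, and readers will take that ratio as the size of the tested effect. The conclusion on independent association rests on the second scale alone.

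**Working it through.** **The plan's own figure.** Section 13.4.2 gives no number. The nearest is the event count in 13.4.1, which is not in dispute. −ln(0.60)/8 = 0.0639 and −ln(0.67)/8 = 0.0501, ratio 0.784. Freedman's formula at one-sided 0.025 and 90% power gives (1.784/0.216)² × (1.960 + 1.282)² = 717; Schoenfeld's gives 710. The stated 716 is reproduced.

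**Inputs for the check.**
- Other-cause death: 0.045 × 32/46 = 0.0313 per year. Prostate cancer death: 0.045 × 14/46 = 0.0137 per year (13.3).
- First failure: 0.12 per year (13.3), used here as the rate of the *other* first failures. A 33% cut gives 0.12 × 0.67 = 0.0804.
- 1779 evaluable patients, 5 years' accrual plus 8 years (13.8.2), so censoring is uniform over 8 to 13 years.
- Assumption: local or distant failure as first event at 0.01 to 0.03 per year. The protocol gives no such rate.

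**Formula.** With constant hazards, endpoint hazard λ and total hazard Λ:
- cumulative incidence F(t) = (λ/Λ)(1 − e^(−Λt));
- event-free probability S(t) = e^(−Λt);
- subdistribution hazard = λ S(t)/(1 − F(t)).

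The subdistribution ratio at time t is therefore the cause-specific ratio × S₁/S₂ × (1 − F₂)/(1 − F₁), with 1 for Arm 1 and 2 for Arm 2.

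**Worked example: endpoint rate 0.02 in both arms (cause-specific ratio 1.00), other first failures cut by 33%.**
- Arm 2: Λ = 0.02 + 0.12 + 0.0313 = 0.1713; S(8) = 0.254; F(8) = (0.02/0.1713) × 0.746 = 8.7%.
- Arm 1: Λ = 0.02 + 0.0804 + 0.0313 = 0.1317; S(8) = 0.349; F(8) = (0.02/0.1317) × 0.651 = 9.9%.
- The subdistribution ratio is 1.00 at time 0, about 1.18 at 4 years, and (0.349/0.254) × (0.913/0.901) = 1.39 at 8 years. The fitted Fine and Gray ratio averages over this path.

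**Fitted ratios** (400,000 simulated patients per arm; power scaled to 1779 patients, one-sided 0.025). Other first failures are cut by 33% and other-cause death is unchanged.

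| True cause-specific ratio | Cause-specific Cox | Fine and Gray |
|---|---|---|
| 1.00 | 1.00 | 1.17 |
| 0.80 | 0.80 | 0.94 |
| 0.67 | 0.67 | 0.79 |

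| Assumed endpoint rate per year | Power at ratio 0.67, cause-specific | Same, Fine and Gray | At ratio 1.00: chance that the Fine and Gray 95% interval lies wholly above 1 |
|---|---|---|---|
| 0.01 | 43% | 18% | 12% |
| 0.02 | 70% | 30% | 19% |
| 0.03 | 85% | 41% | 25% |

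A separate trial-by-trial simulation gave 42/73/86% against 16/31/40% for the two power columns.

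**Where it does not matter much.**
- Disease-specific survival, other-cause death unchanged: cause-specific 0.67 gives 0.67 on Fine and Gray's scale, with power of about 72% on both.
- The same endpoint at a true ratio of 1.00: the Fine and Gray ratio is 1.035 if other-cause death falls by 20% and 0.964 if it rises by 25%. The shift can go either way.
- PSA failure at 0.12 per year with only other-cause death competing: 0.67 gives 0.685.
- Distant failure with only other-cause death competing and unchanged: 0.67 gives 0.67 to 0.68.

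**The case against.** **The decision rule is fixed and consistent.** Each of these endpoints is tested by the cause-specific log-rank test at 0.025. Fine and Gray's model carries no alpha and no success criterion, and it has no role for overall survival or DFS. This stands. A reader might infer that the secondary tests are invalid or their error rate inflated; the text does not support that.

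**Fine and Gray's model is not giving false findings of harm.** In the worked example cumulative incidence really is higher in Arm 1 (9.9% against 8.7%), so the 12% to 25% are not error rates for the model's own null. This also stands. The fault is that the model answers a question other than the tested one.

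**The sign rarely turns.** With a true cause-specific ratio of 0.67 and an endpoint rate of 0.02, the Fine and Gray ratio is 0.97 when other failures are cut by 70% and 1.02 when they are cut by 80%. A reader might infer that a real benefit would commonly be reported as harm; attenuation is the realistic consequence.

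**Death as the only competing event.** One could enter the 13.4.1 death rates (0.0639 against 0.0501) as the competing rates and leave failure unaffected; this gives a Fine and Gray ratio of about 1.07. But 13.8.1 routes the expected benefit through prostate cancer death: a 33% reduction there becomes an average 11% in all deaths (with the 13.3 split, 0.33 × 14/46 = 10%). Death before any failure is then mainly other-cause death, which that translation leaves unchanged, and the gap closes. This scenario should not carry the point.

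**The size depends on what counts as another failure.** That is so, and the larger figures hold only if PSA or other first failures compete with local or distant failure. That is, however, how 13.4.2 words its censoring.

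**The unadjusted ratio is not expressly assigned to Fine and Gray's model.** Correct: it follows from sentence order only. The adjusted question is assigned to it outright.

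**The statistical analysis plan could add a Cox model.** It could, but the protocol itself names the regression, and names another one.

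**Conclusion.** The point holds as a mismatch between test and estimate inside 13.4.2. Six endpoints are tested on cause-specific hazards, while the only regression named for them, for the adjusted conclusion and apparently for the hazard ratios, works on cumulative incidence. The planned tests, the primary endpoint and DFS are untouched.

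The difference is material for local progression and distant failure, on three conditions: other first failures are censored as competing events, TAS cuts them by about a third from 0.12 per year, and the endpoint occurs first at an assumed 0.01 to 0.03 per year. If the 0.12 is read to include the endpoint itself, the competing rate is lower and the shift somewhat smaller. For disease-specific survival with other-cause death unchanged the gap is negligible, and for PSA failure with only other-cause death competing it is small. No size was worked out for the second relapses. If TAS raised the competing events, the shift would reverse and flatter TAS.

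This merits a correction to the text, because the paragraph's own argument points to the model that it leaves out.

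**What to change.** In 13.4.2, name a cause-specific Cox model, with the same censoring as the log-rank test, as the source of the unadjusted and adjusted hazard ratios and of the conclusion on independent association, for all six endpoints. Keep Fine and Gray's model as a supplementary analysis of cumulative incidence, labelled as such and shown with the treatment effect on the competing events. Because the Cox model takes over whatever censoring the log-rank test uses, estimate and test stay aligned however the competing events are defined.

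The cost is one or two sentences and one extra model per endpoint, with no new data. The downside is that two ratios per endpoint are shown and must be clearly labelled.

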#### **13.4.3 Prostate Re-Biopsy at Two Years**

Because an endpoint in this study is local progression, a biopsy of the prostate will be obtained at two years (24 months) following completion of radiation therapy. The rate of prostate re-biopsy at two years is defined as the proportion of patients whose results are positive among all eligible patients. This rate will be estimated in each arm separately.

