### **2.2 Secondary Objectives**

- 2.2.1** To compare the rates of disease-specific survival, clinical relapse (local progression and/or distant failure), freedom from PSA failure, freedom from second clinical relapse, freedom from second PSA relapse, and disease-free survival
- 2.2.2** To compare the prostate re-biopsy at two years
- 2.2.3** To measure the effect on sexual function

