### **8.2 Prostate Re-biopsy**

- 8.2.1** The two-year biopsy will be performed for any patient who has achieved a clinical complete response (*NED*) or an equivocal disease response (*ED*) unless there is a medical contraindication to rebiopsy or definite evidence of local progression by clinical physical exam.
- 8.2.2** If the patient has distant metastatic disease or is post orchiectomy, the biopsy will not be performed.

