The study was designed for three interim analyses of the primary endpoint, disease-specific survival (death due to prostate cancer) when we observe 29% (76), 60% (157) and 80% (209) of the 260 required maximum number of prostate cancer related deaths. D'Amico et al showed a statistically significant improvement in disease-specific survival with six months of total androgen blockade given two months before, during and after radiation therapy in a similar patient population. Based on this result, the disease site and study chairs requested an early look at disease-specific survival. This request was presented at the RTOG Data Monitoring Committee (DMC) in June 2005. The RTOG DMC approved an early analysis of the primary endpoint. Thus the first interim analysis is now planned to be done with 66 deaths. The boundary for early stopping (or the nominal significance level for the test) will be a modified Haybittle-Peto boundary. The stopping boundary of each of the three interim analyses is 3.291 (for a nominal significance level of 0.001) and the boundary for the final analysis is 1.96 which makes the overall significance level 0.051.

**All eligible patients who are randomized to the study will be included in the comparison of treatment arms (intent-to-treat analysis).**

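### The two-year re-biopsy rate keeps men without a biopsy in its denominator, so it mixes biopsy uptake with tumour clearance and scores known local failures like negative biopsies

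*Protocol*

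**What the plan says.** Section 13.4.3 gives an explicit numerator and denominator: the rate is "defined as the proportion of patients whose results are positive among all eligible patients". It adds "This rate will be estimated in each arm separately" and has no rule for a man without a biopsy result.

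Section 8.2 decides who is biopsied. Section 8.2.1 begins "The two-year biopsy will be performed for any patient who has achieved a clinical complete response", extends this to equivocal disease, and then makes exceptions: "unless there is a medical contraindication to rebiopsy or definite evidence of local progression by clinical physical exam". Section 8.2.2 adds a further exclusion: "If the patient has distant metastatic disease or is post orchiectomy, the biopsy will not be performed".

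Section 13.4 shows how the statistical section uses the word eligible: "All eligible patients who are randomized to the study will be included in the comparison of treatment arms". That is the randomized trial population, not the men who qualify for biopsy.

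The endpoint is meant for a comparison. Objective 2.2.2 reads "To compare the prostate re-biopsy at two years", and section 13.2.2.8 lists it among the secondary endpoints. Section 11.2.7 gives tumour clearance and local control as the reason for the biopsy.

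**The concern.** Read together, sections 8.2 and 13.4.3 place a group of men in the denominator who cannot contribute to the numerator. Some are missing for reasons that may have little to do with the tumour, such as refusal, a contraindication or death from another cause. Others are missing because the disease has already declared itself, through "definite evidence of local progression by clinical physical exam" or through metastasis. The formula treats both kinds like men whose biopsy was clear.

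The endpoint is meant to describe clearance of tumour from the prostate. As defined, it can move because biopsy was done more often in one arm, or because one arm had more men removed from biopsy by clinical failure. A reader of the final report could not separate these from a real difference in clearance.

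**Working it through.** The protocol states no expected re-biopsy rate, uptake, power or significance level for this endpoint, so there is no planned figure to reproduce. The definition can be written as a formula and tested under assumed values.

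**Inputs.** Section 13.8.2 requires 1779 evaluable patients, so 1779/2 ≈ 890 per arm. Everything else is assumed:
- f: share of an arm barred from biopsy by documented clinical failure
- m: share of the remainder not biopsied for any other reason
- p: share positive among those biopsied

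**Formula.** Rate under section 13.4.3 = (1 − f)(1 − m)p. It falls as f rises and as m rises, whatever the tumour is doing. The quantity that describes the biopsied men is p.

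**Unequal uptake only.** Take p = 30% in both arms and 70% versus 55% of all men biopsied.
- 0.70 × 0.30 = 21.0%; 0.55 × 0.30 = 16.5%; difference 4.5 points
- Unpooled standard error = √[(0.21 × 0.79 + 0.165 × 0.835)/890] = 0.0185, so z = 2.44 and two-sided p = 0.015
- A smaller gap, 70% versus 60% biopsied, gives 21% versus 18%

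Positivity is identical, so the whole difference is uptake.

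**Unequal clinical failure only.** Take f = 5% versus 10%, m = 40% and p = 30% in both arms.
- Section 13.4.3 rate: 0.95 × 0.60 × 0.30 = 17.1% versus 0.90 × 0.60 × 0.30 = 16.2%. The arm with twice the failures reads 0.9 points lower.
- Positives among the biopsied: 30% versus 30%.
- Failures counted as not cleared (treating all of f as local progression): 0.05 + 0.171 = 22.1% versus 0.10 + 0.162 = 26.2%. The same arm now reads 4.1 points higher.

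A grid was run over f of 2% vs 5%, 5% vs 10% and 5% vs 15%, m from 0 to 60%, and p from 20% to 40%. The section 13.4.3 rate favoured the arm with more failures by 0.2 to 4.0 points. Counting failures as not cleared reversed the sign in every cell, to 1.8 to 9.2 points against that arm.

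**Unequal positivity.** Take p = 20% versus 40% with 50% versus 35% of all men biopsied: 0.50 × 0.20 = 10% versus 0.35 × 0.40 = 14%. A 20-point difference among the biopsied shrinks to 4 points, but its direction survives. With equal m, the ranking turns back once p₂ exceeds p₁(1 − f₁)/(1 − f₂). For p₁ = 30% and the three failure pairs above, that threshold is 30.9% to 33.5%.

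**Check of an obvious repair.** One could count a positive biopsy or local progression as failure among men evaluable for either. Take 10% local progression and p = 30% in both arms, so true local failure is 0.10 + 0.90 × 0.30 = 37% in each. With 70% versus 55% of the remaining men biopsied:
- (0.10 + 0.90 × 0.70 × 0.30)/(0.10 + 0.90 × 0.70) = 0.289/0.730 = 39.6%
- (0.10 + 0.90 × 0.55 × 0.30)/(0.10 + 0.90 × 0.55) = 0.2485/0.595 = 41.8%

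Every man with progression is evaluable, but the others are evaluable only if biopsied. Low uptake therefore inflates the failure rate. This repair does not remove the problem.

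**The case against.** **The failures are counted elsewhere.** Local progression and distant failure are secondary endpoints in their own right (section 13.2.2) with their own log-rank tests (section 13.4.2). This is true, and the trial does not record these men as tumour-free. It limits the damage to the re-biopsy endpoint but does not make that rate interpretable.

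**Eligible could mean eligible for biopsy.** Section 13.4.3 does not say randomized, and section 8.2 does define who qualifies for biopsy. The usage in section 13.4 makes this the less likely reading. It would take the clinical failures out of the denominator, but men who decline or miss the biopsy would still count as not positive. The wording needs repair either way.

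**No test is attached.** Section 13.4.3 only estimates the rate by arm, whereas sections 13.4.2 and 13.4.4 set significance levels. The p-value above is thus illustrative and is not one the plan would produce. Objective 2.2.2 still calls for a comparison, and two separately estimated rates will be read as one.

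**Leave it to the analysis plan.** Missing-biopsy handling often belongs there. Here, though, the protocol has already fixed a denominator that conflicts with its own biopsy rules.

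**A stronger reading.** A reader might infer that the arm with more failures will look better, or that the rule works against androgen suppression. The documents do not support that as a fact. It follows only if positivity and other uptake are equal. An arm with more clinical failures may well also have more positive biopsies, and a few extra points of positivity restore the ranking. Unequal uptake could run in either direction.

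**Conclusion.** The definition is faulty as written. Sections 8.2 and 13.4.3 alone show that men without a biopsy, known local failures among them, lower the reported rate just as negative biopsies do. With equal positivity and equal other uptake, the bias favours the arm with more clinical failures. With unequal positivity it attenuates or distorts the difference.

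The actual size cannot be stated. In the assumed cases above, the artefact ranges from a fraction of a point to about 4 points when failure exclusions alone differ, and reaches 4.5 points for a 15-point gap in uptake. These figures rest on assumed uptake, exclusion and positivity, none of which the protocol supplies.

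Importance is moderate: one secondary endpoint, with no power or significance level attached and no effect on the overall survival analysis.

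**What to change.** Leave the biopsy rules in section 8.2 as they are and rewrite section 13.4.3:

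1. Define the re-biopsy rate as positives among men with an evaluable 24-month biopsy.
2. Report by arm the number biopsied and the reasons for no biopsy (local progression, metastasis, orchiectomy, contraindication, death, refusal, missed).
3. For the arm comparison, add an analysis over all eligible patients in which documented local progression by two years or a positive biopsy counts as local failure. For men without local progression who were not biopsied, give sensitivity bounds (all failed, none failed), or use weighting or imputation. Do not restrict to men evaluable for either component.
4. Name one time origin for the two-year point. Section 11.2.7 times the biopsy from the end of radiotherapy, while section 11.3.8 times local progression from randomization.

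The cost is one paragraph and one table. Section 12.0 already collects re-biopsy reports and follow-up forms at progression; some reasons for no biopsy may have to be drawn from follow-up records.

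There are two downsides. The biopsied men are a selected group, which the uptake table will show. The bounds will be wide if uptake is low: in the case of f = 5% and m = 40%, they run from 22.1% to 22.1% + 0.95 × 0.40 = 60.1%. That width is the honest statement of what the biopsies can tell.

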### **13.2.2 Secondary Endpoints**

**13.2.2.1** Disease-specific survival (See section 11.3.11)

**13.2.2.2** Local progression (See section 11.3.8)

**13.2.2.3** Distant failure (See section 11.3.9)

**13.2.2.4** Freedom from PSA failure (See section 11.3.6)

**13.2.2.5** Freedom from second clinical relapse (local progression and/or distant failure)

**13.2.2.6** Freedom from second PSA relapse (See section 11.3.7)

**13.2.2.7** Disease-free survival (See section 11.3.4)

**13.2.2.8** Prostate re-biopsy at two years

**13.2.2.9** Effect on sexual function (See section 11.3.12)

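### The two-year re-biopsy is to be compared between arms under objective 2.2.2, but section 13.4.3 plans only a separate estimate per arm; first clinical relapse in 2.2.1 also needs aligning with the endpoint list

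*Protocol*

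**What the plan says.** **Re-biopsy.** Secondary objective 2.2.2 is "To compare the prostate re-biopsy at two years". The outcome is listed in section 13.2.2 as "Prostate re-biopsy at two years". Section 13.4.3 defines the rate as "the proportion of patients whose results are positive among all eligible patients" and closes with "This rate will be estimated in each arm separately". No other section adds a between-arm analysis of it. Section 8.2 exempts some men from the biopsy: those with a medical contraindication, definite local progression on examination, distant metastases or orchiectomy.

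**Clinical relapse.** Objective 2.2.1 is to compare rates of several outcomes, among them "clinical relapse (local progression and/or distant failure), freedom from PSA failure". Section 13.2.2 lists local progression and distant failure as two endpoints and gives the composite only as second clinical relapse. Section 13.4.2 follows the same list: "disease-specific survival, local progression, distant failure, PSA failure, second clinical relapse", then second PSA relapse. Each is tested between arms by log-rank at 0.025, and a man whose first failure is of another type is censored.

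**The concern.** An objective worded as a comparison needs an analysis that compares. Two rates reported side by side do not state the size of the difference or its uncertainty, and the method of comparing them could then be chosen after the results are known. The biopsy is an invasive procedure, and 13.4.3 is the only stated between-arm use of its result, since section 11.3.8 determines local progression by clinical examination.

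For clinical relapse less is at stake. The objective names one event, and the endpoint list has a second such event without the first. A reader cannot tell whether the composite or its two components answers the objective.

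**Working it through.** The protocol states no figure for either outcome, so there is nothing to reproduce. The finding rests on setting the sections side by side.

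| Outcome | Objective | Planned between-arm analysis |
|---|---|---|
| Disease-free survival | 2.2.1, compare | Log-rank at 0.025, Cox model (13.4.2) |
| Local progression, distant failure | 2.2.1, as parts of clinical relapse | Log-rank at 0.025 each, adjusted regression (13.4.2) |
| First clinical relapse (composite) | 2.2.1, compare | None; only second clinical relapse is listed |
| Erectile function (yes/no) | 2.2.3, measure effect | Two-sample test of proportions at 0.05 (13.4.4) |
| Re-biopsy at two years | 2.2.2, compare | None; one estimate per arm (13.4.3) |

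The other binary secondary outcome has a test in the very next section, and 2.0, 13.2 and 13.4 all carry the 7/14/08 revision date. The mismatch therefore sits within one revision.

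**Could the data support a re-biopsy comparison?** Assumed inputs, none from the documents: 300 or 600 men biopsied per arm, 30% versus 20% positive.

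- SE = √(0.3×0.7/n + 0.2×0.8/n); half-width = 1.96×SE; power = Φ(0.10/SE − 1.96).
- n = 300: SE 0.0351, half-width 6.9 points, power 81%.
- n = 600: SE 0.0248, half-width 4.9 points, power 98%.

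**The denominator matters.** Section 13.4.3 divides by all eligible men. With about 890 evaluable per arm (1779/2, section 13.8.2) and the same assumptions:

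- 300 biopsied: 90/890 = 10.1% versus 60/890 = 6.7%; half-width 2.6 points, power 73%.
- 600 biopsied: 180/890 = 20.2% versus 120/890 = 13.5%; half-width 3.5 points, power 97%.

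The all-eligible rate equals the share biopsied times the proportion positive among those biopsied. As a deliberately extreme case, take 600 biopsied in one arm and 300 in the other, with 30% positive in both. The rates become 20.2% and 10.1%, a difference produced wholly by who was biopsied. Men exempted under 8.2 for local progression would count as not positive, so the arm with more local failures could look better.

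**Clinical relapse.** Illustration on assumed counts of 140 local and 105 distant first events. Under the censoring in 13.4.2 these do not overlap, apart from simultaneous failures, so the composite has about 140 + 105 = 245. For a 33% hazard reduction (the size that 13.8.1 assumes for prostate cancer death, borrowed here), power = Φ(√(d/4)×|ln 0.67| − 1.96):

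- d = 140: 66%. d = 105: 54%. d = 245: 88%.

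The gain for the composite holds only if both components have a similar effect.

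**The case against.** The strongest case against the re-biopsy point is that estimating a rate per arm is the first step of a comparison and does not exclude one. Section 13.1 says the objectives are met by a randomized comparison of two groups, and the choice of test for a low-ranked binary outcome is often left to a statistical analysis plan, which is not shown here. Given both rates and their denominators, anyone can compute a difference. This lowers the weight of the point but does not remove it. The protocol is not silent here: it states the analysis, and what it states stops short of its own objective, unlike its treatment of the other secondary outcomes.

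On clinical relapse the objection largely succeeds. A reader might infer that neither objective gets any between-arm comparison. The documents do not support that. Local progression and distant failure are both listed, defined and log-rank tested at 0.025 with hazard ratios, and the and/or in 2.2.1 can be read as covering each. Disease-free survival, also tested, includes both events. What stands is narrower: the composite has no endpoint line and no test. The component tests do not replace it, because each censors men who first fail in another way, and disease-free survival adds PSA failure and death from other causes.

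It is also fair that simply adding a test to the rate as 13.4.3 defines it could mislead, for the denominator reason shown above.

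**Conclusion.** For the re-biopsy the point holds: 2.2.2 promises a comparison and 13.4.3 plans none. This conclusion is textual and needs no assumed figure. It concerns a secondary outcome, leaves the primary analysis untouched and should be corrected because the correction is cheap.

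For clinical relapse there is only an alignment gap between 2.2.1 and sections 13.2.2 and 13.4.2. The components are compared; the composite first relapse is not.

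The interval widths and power figures are illustrations on assumed biopsy numbers, positivity rates and event counts. They show that a re-biopsy comparison could be informative, not what this trial would find.

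**What to change.** **Section 13.4.3.** Replace the closing sentence with wording to this effect: *The arms will be compared among men biopsied by the difference in the proportion positive, with its 95% confidence interval and a test stratified by the randomization factors (PSA, differentiation, nodal status). The number biopsied and the reasons for no biopsy will be reported by arm. A sensitivity analysis will cover all eligible men, in which men not biopsied because of local progression are not counted as negative.* The all-eligible definition of the rate in that section must be revised to match. The comparison among biopsied men is not fully randomized and should be labelled so. If no comparison is intended, 2.2.2 should instead be reworded to estimation.

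**Sections 2.2.1, 13.2.2 and 13.4.2.** Either add time from randomization to first clinical relapse (the earlier of local progression and distant failure), with a log-rank comparison and hazard ratio, and keep the component tests; or reword 2.2.1 to name local progression and distant failure separately.

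**Cost.** Wording and a few further analyses, with no extra patient or biopsy. The data forms listed in section 12.0 do not show whether the reason for no biopsy is recorded, so some may have to be recovered from follow-up records.
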